#### Secondary outcome - mobility

The level of mobility will be quantified using the Gross Motor Function Measure 66 Item Set (GMFM-66 IS) [34] by a certified assessor. GMFM-66 IS scores will be calculated with the corresponding software (Gross Motor Ability Estimator version 1.0) that calculates scores on an interval scale.

#### Patient characteristics

Patient characteristics will be recorded using an intake form and will include age, gender, race, ethnicity, weight, length, localisation of CP (uni- or bilateral) and Gross Motor Function Classification System (GMFCS) [35] class. To asses problematic behaviour of the child, the strength and difficulties questionnaire (SDQ) [36] will be filled in by the parents. In addition, questions will also be asked about the children's sport activities, current therapies and other treatments, as well as preference sleeping positions.

#### Physical examination

Physical examination will be performed by the assessor to evaluate the physical characteristics of the patient. Variables to be measured are: 1) Position of the foot in standing, 2) transmalleolar axis position [37], 3) gait pattern classification according to Rodda [38] and Becher [39], 4) ROM of the ankle and knee joints, 5) spasticity, by measuring the angle of catch (AOC) [40] of the ankle and knee, 5) selective motor control, using the Selective Control Assessment of the Lower Extremity (SCALE) [41] and 6) lower leg length. For all participants, the physical examination related outcome measures will only be measured in the potentially treated legs.

#### Protocol adherence

Web based diaries will be used to record the protocol adherence and will be collected by a research assistant. These diaries will be filled in during the fourth week of each month and include questions regarding KAFO use, KAFO-related complaints, sleeping problems, the use of an ankle-foot orthosis (AFO) as well as questions regarding stretching exercises performed over the last month. Problems with KAFO use experienced by patient and/or parents will be monitored by specific diary questions. The research assistant will call the participants at least once a month to check if there are any problems with the KAFO or motor function of the participant. Reported problems will be solved as soon as possible.

Furthermore, to check the reliability of diary reported KAFO wearing time, wearing time of the splints (for a subgroup of 10 children, recruited at VU University Medical Center) will be determined on the basis of KAFO temperature measured using a TidBit temperature datalogger (UTBI-001, Onset Computer Corporation, Bourne, MA). The KAFO temperature will increase due to body heat when the KAFO is worn. A sample of KAFO temperature data will be recorded each 15 minutes during the treatment period. Parents and children are not informed about the purpose of this measurement.

#### Other

To get an indication of the sustained muscle stretch that is applied by the KAFOs, two measurements will be added. 1) The ankle moment at a *γ_(f-t) _of *0° to simulate the static KAFO condition. This condition will be performed before the handheld dynamometer protocol. 2) The ankle dorsiflexion angle that could be imposed by the dynamic KAFO will be estimated during consultation hours by the physician using a goniometer.

### Morphological part

To determine muscle morphology related variables, 3D-ultrasound imaging will be performed on the *medial Gastrocnemius muscle*. This muscle, covered with an ultrasound gel, will be scanned along it's length (making multiple transverse cross-section images, see Figure 6) using a 5-cm linear array probe (12,5 MHz) of a B-mode ultrasound device (Technos MPX, ESAOTE, Italy). Two sets of recordings of the *medial Gastrocnemius muscle *will be made for each session. During 3D-ultrasound measurements, the position of the probe with a cluster marker is recorded using an active 3D marker motion analysis system (Optotrak, Northern Digital, Waterloo, Canada). In addition, 6 anatomical landmarks (lateral malleolus, medial malleolus, medial femur condyle, lateral femur condyle, medial femur epicondyle and lateral femur epicondyle) are recorded before each experiment to gain an anatomical frame of reference for post experimental 3D image reconstruction. In a prone position, the children are lying quietly on a bench. Using the ankle dynamometer, the ankle is fixed at *γ_(f-t) _*corresponding to 0, 1 and 4 Nm net dorsal flexion moment. Muscle activity is checked using EMG during the ultra sound measurements as described above in the primary outcome section.

**Figure 6 F6:**
[figure not shown]
**Path of the ultrasound probe during scanning the *medial Gastrocnemius muscle *(MGM)**. The probe follows the path over the black line. It starts proximal, with the probe perpendicular to the path. First, the probe will be guided from lateral to medial over the respectively lateral and medial condyle of the femur. Then the probe will be rotated and moved to distal between the medial and lateral border of *medial Gastrocnemius muscle *belly towards the distal end of the muscle belly, the *Gastrocnemus muscle *(GM) tendon and the calcaneus.

The ultra sound images will be converted into a voxel array and 3D-reconstructions will be calculated using a custom made program in MATLAB software according to the method that was described by Bénard e.a.[42]. Measurements are performed in the mid-longitudinal fascicle plane of the *medial Gastrocnemius muscle*, being perpendicular to (the tangent of) the distal aponeurosis of the *medial Gastrocnemius muscle*, selected from the voxel array (see Figure 7). The use of the correct plane is essential for minimizing measurement errors of fascicle length, fascicle angle and muscle thickness [43]. Measurements are performed five times because this number of repetitions has been shown to yield reliable results [43].

**Figure 7 F7:**
[figure not shown]
**The orientation of the mid-longitudinal fascicle plane**. Three orientation items (*) were used to define the mid-longitudinal fascicle plane of the *medial Gastrocnemius muscle *(MGM) (shaded plane and inset): 1) The estimate of the origin of the *medial Gastrocnemius muscle *(at 1/4^th ^of the line from medial to lateral condyle of the femur, see inset **A**) 2) the most distal muscle belly end, and 3) a point on the line perpendicular to tangent to the distal aponeurosis in the transversal plane. The direction of the tangent is determined in the distal part of the *medial Gastrocnemius muscle *belly exactly in between the *medial Gastrocnemius muscle *borders (see inset **B**).

The following variables will be measured: tendon length (ℓ_t_,) muscle length (ℓ_m_), fascicle length (ℓ_(fasc)_), muscle thickness (ℓ_(m th)_) and fascicle angles with the aponeuroses (*γ_(fasc)_)*.

Using trigonometry, the following variables will be calculated: length of *medial Gastrocnemius muscle *intramuscular distal (i.e. deep) and proximal (i.e. superficial aponeuroses) (ℓ_a_) and length component of the physiological cross-section (ℓA_f_, the added perpendicular diameters of fascicles within the mid-longitudinal fascicle plane, Figure 8).

**Figure 8 F8:**
[figure not shown]
**Measurement and calculation of muscle geometry of *medial Gastrocnemius muscle *within its mid-longitudinal fascicle plane**. (**A**) The mid-longitudinal fascicle plane, determined with 3D ultrasound. The *medial Gastrocnemius muscle *(MGM) is covered by the subcutis (SUB) and supported by *Soleus muscle *(SM). Parts of both femur (fem) and tibia (tib) are shown. The black dotted lines define the outline of the muscle. The most distal muscle belly end is indicated by a black arrow. The length of the target fascicle (ℓ_(fasc)_) (dashed black line), centred at 2/3^rd ^(*) of muscle belly length (from the origin) is measured. Muscle thickness (ℓ_(m th)_) was calculated as the distance between the proximal and the distal aponeurosis at the proximal end of the target fascicle (left black double arrow). The fascicle-aponeurosis angle (*γ_(fasc)_) *was calculated as the mean of the angles of the fascicle with the proximal and distal aponeurosis (black arcs). Scale bar depicts 1 cm. (**B**) Schematic overview of morphological muscle parameters in the mid-longitudinal fascicle plane of the *medial Gastrocnemius muscle*. The length of the aponeurosis (ℓ_a_) and the length of the physiological cross-sectional area (ℓ_Af_) will be calculated from this model. The muscle belly length (ℓ_m_) will be measured from the origin at the femur condyle to the distal end of the muscle belly. The tendon length (ℓ_t_) will be measured from the distal muscle belly end to the insertion at the calcaneus.

In case of potential bilateral treatment, the morphological outcome measures will only be measured on the participant's most involved leg. In case of potential unilateral treatment, the morphological outcome measure will only be measured at the participant's potentially treated leg.

### Exit criteria

#### Withdrawal

The investigator and/or clinician can decide to withdraw a subject from the study for urgent medical reasons. First, they have an ankle dorsiflexion angle with an extended knee, measured as the angle between tibia and footplate (*γ_(f-t)_)*, of 10° plantar flexion or more when an external ankle dorsiflexion moment of 4 Nm is applied. In such a case, the assessor will refer the child to the clinician who will decide whether the reduction in ROM has to be treated or not (note that the net ankle dorsiflexion moment of 4 Nm applied by the assessors is lower than is typically applied in a clinical setting). These children will not undergo follow-up measurements as they will receive other treatment for impaired ROM. Second, children have irresolvable problems with KAFO use (pain, pressure sores, sleeping problems). These subjects will be asked to undergo measurements after withdrawal and will be included in the analyses. Third, children can decide to withdraw at any time for any reason. These children will be asked to undergo measurements after withdrawal as well and will also be included in the analyses.

#### Premature termination of the study

The effects of orthotic management in rest on ankle dorsiflexion at full knee extension will be evaluated as soon as measurements have been performed on 30 children regarding follow-up measurement of 6 months. If the children in the control group show significantly larger *γ_(f-t) _*reduction compared to the other groups, this group will also be treated with a knee-ankle-foot orthosis. If the knee-ankle-foot orthoses groups (static and/or dynamic) show significantly larger reductions in *γ_(f-t) _*than the control group, the study will be terminated.

### Randomization

Randomisation will be performed by block randomisation of 3, 6 or 9 subjects, with pre-stratification by center. A member of the project team ([name]) not being involved in the recruitment/inclusion procedure of the subjects and not being involved in measurements will randomly generate an allocation sequence before the start of the trial to perform the randomisation. The order of allocation of treatment will be noted by [name] and kept in numbered sealed envelopes. After checking the inclusion and exclusion criteria by a physician and after receiving informed consent of the participant's parents, treatment allocation will be established by the research assistant after opening the numbered envelope. Subjects will be informed about their allocation after performing their baseline measurement.

### Blinding

The researchers performing the measurements and analysing the data will be blinded with respect to the treatment allocation. The children and their parents will be instructed to give no information about their treatment to the assessors. Blinding will be evaluated at the end of the study by asking the researchers the question: "In which group is the subject allocated and do you know this for sure, or is this a guess?"

### Statistics

Statistical analysis will be performed according to an "intention to treat" principle. All relevant subject characteristics, such as age, body weight and length, gender, clinical diagnosis, will be described by their mean value and standard deviation, or percentages. Differences between groups at baseline will be tested using linear regression techniques or Chi-square statistics. The effect of the intervention will be analysed using a multi-level analysis, with the primary and secondary outcome measures as dependent variables and treatment group and time as independent variables. To test for any differences in the changes of variables between groups, a treatment*time interaction is included as independent variable. Analysis are adjusted for treatment site (Amsterdam, Arnhem or St Louis). Covariates will be: 1) KAFO wearing time, 2) lower leg growth, 3) use of an AFO by day, 4) stretching exercises and 5) level of spasticity. The α-value will be set at 0.05.

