#### Sample size calculation

Expecting a 5 degree change in ankle ROM (assumed as clinically relevant), with a standard deviation of 4.5 degrees, a significance level (α) of 0.05 that is corrected for comparisons between three groups using a Bonferroni correction (α = 0.0167), and a power level of 80%, 13 children in each group will be sufficient. The calculation takes five repeated measurements with a correlation coefficient of ρ = 0.7 into account. In this study, 66 participants (22 in each group) will be recruited to allow drop outs.

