### Setting & design

A single blind randomized controlled trial will be performed at the three above mentioned centers. The participants will be assigned into 3 different groups. In addition to their regular treatment, two groups will be treated with a dynamic or static KAFO for one year to prevent for a reduction of ankle dorsiflexion at full knee extension and one group will be included as a control group without additional intervention. The morphological measurements will be performed only at Dutch participants at the VU University medical center.

Measurements will be performed at baseline and at 3, 6, 9 and 12 months after treatment allocation. In combination with those measurements, participants of the experimental groups will have a meeting with the orthotist and physician to check for complications with the KAFO.

The assessor and analyser are blinded for treatment allocation. The trial will be performed between January 2010 and December 2012.

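### The multi-level model tests an unadjusted difference in change and so gives up precision: about 15% of variance (8% of standard error) at the plan's own correlation of 0.7

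*Protocol article*

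**What the plan says.** The Statistics section of the protocol article describes a multi-level analysis "with the primary and secondary outcome measures as dependent variables and treatment group and time as independent variables". The term that carries the treatment comparison is named: "To test for any differences in the changes of variables between groups, a treatment*time interaction is included as independent variable". The model is adjusted for site, and the covariate list is closed: "Covariates will be: 1) KAFO wearing time, 2) lower leg growth, 3) use of an AFO by day, 4) stretching exercises and 5) level of" (the fifth item is spasticity). The baseline value of the outcome is not on it.

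Baseline belongs to the repeated outcome. The visit schedule under Setting & design reads "Measurements will be performed at baseline and at 3, 6, 9 and 12 months after treatment allocation", which makes five visits, and the Sample size calculation says "The calculation takes five repeated measurements with a correlation coefficient of ρ = 0.7 into account". The only other mention of baseline in the Statistics section is that "Differences between groups at baseline will be tested using linear regression techniques or Chi-square statistics".

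**The concern.** With baseline in the outcome vector and a free treatment main effect, the model estimates a separate baseline mean for each arm. The interaction then compares raw changes from those means. In a randomised trial the true baseline means are equal, so the model spends information on estimating differences known to be zero. An analysis that uses this knowledge, by baseline adjustment or a common baseline mean, estimates the same treatment effect with a smaller variance whenever the correlation between visits is below 1 and variances are equal.

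What is at stake is the width of the confidence intervals for the primary and secondary outcomes in a small three-arm paediatric trial, and some power if dropout is heavy.

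**Working it through.** **Inputs from the Sample size calculation.** "Expecting a 5 degree change in ankle ROM (assumed as clinically relevant), with a standard deviation of 4.5 degrees"; α = 0.0167; power 80%; five measurements; ρ = 0.7; 13 per arm required; 22 per arm recruited. The article does not say whether 4.5 degrees is the SD of one measurement or of a change, so both readings are shown. Two-sided α is assumed.

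**The plan's own figure.** For one measurement, n = 2 × [4.5 × (2.393 + 0.842)/5]² = 16.95. The equal-correlation factor is [1 + (5 − 1) × 0.7]/5 = 0.76. The product is 12.88, which rounds up to 13. The stated size reproduces, so equal correlation between visits is the plan's working assumption.

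**Variance of the month-12 contrast**, in units of σ² (variance of one measurement), with equal variances and equal correlation:

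- As written (difference in change): 2(1 − ρ) = 2 × 0.3 = 0.60
- Baseline-adjusted: 1 − ρ² = 1 − 0.49 = 0.51
- Reduction: 1 − 0.51/0.60 = 15%, which is (1 − ρ)/2
- Reduction in standard error: 1 − √0.85 = 7.8%
- Equivalent arm size: 22/0.85 = 25.9

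Generalised least squares on the full three-arm, five-visit model gives 0.60 and 0.51. A simulation of 20,000 trials with 22 per arm, adjusting for baseline as a covariate, gives a reduction of 15.3%.

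**Coding of time.** The article does not state it. A linear slope gives 0.480 against 0.415, a reduction of 13.6%. The mean of the four follow-up visits gives 0.375 against 0.285, a reduction of 24%.

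**Sensitivity to ρ at month 12:**

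| ρ | Reduction in variance |
|---|---|
| 0.5 | 25% |
| 0.6 | 20% |
| 0.7 | 15% |
| 0.8 | 10% |
| 0.9 | 5% |

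**Sensitivity to unequal variances.** Let k be the follow-up SD divided by the baseline SD. The factors become 1 + k² − 2ρk (change) and k²(1 − ρ²) (adjusted). At ρ = 0.7:

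- k = 1.1: 0.670 against 0.617, a reduction of 7.9%
- k = 1.2: 0.760 against 0.734, a reduction of 3.4%
- k = 1/0.7 = 1.43: no reduction

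The document does not give k; these values are illustrations.

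**Power** = Φ(5/SE − 2.393), with SE = s√(2/n) and α = 0.0167:

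| 4.5° read as | Analysis | s (degrees) | SE, n = 22 | Power, n = 22 | Power, n = 13 |
|---|---|---|---|---|---|
| SD of one measurement | change | 4.5√0.60 = 3.49 | 1.05 | 99.1% | 89.7% |
| SD of one measurement | adjusted | 4.5√0.51 = 3.21 | 0.97 | 99.7% | 94.2% |
| SD of change | change | 4.50 | 1.36 | 90.2% | 67.0% |
| SD of change | adjusted | 4.5√0.85 = 4.15 | 1.25 | 94.6% | 75.2% |

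Site and the other covariates are left out of these calculations.

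**The case against.** The strongest reply is that nothing here is wrong. The interaction matches the hypothesis of a smaller decline, and under randomisation it is unbiased with a valid type I error. Choosing a baseline-adjusted model is a matter of efficiency, and details of parameterisation may sit in a fuller plan. The first part stands. The second stands only in part: the article names the terms and closes the covariate list, so leaving out the baseline value is a stated choice.

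The size also needs restraint. The 15% is a variance figure that rests on equal variances. Entry is limited to dorsiflexion between 0 and 20 degrees, and follow-up is not limited in the same way, so a larger SD at follow-up is plausible and would shrink the gain. A correlation that decays with time would raise it: 38% if adjacent visits correlate at 0.7 and the baseline-to-month-12 correlation is 0.7⁴ = 0.24. That is not the structure behind the plan's sample size.

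A reader might count chance baseline imbalance as a second harm. If 4.5 degrees is the SD of one measurement, the SE of a baseline difference between two arms is 4.5 × √(2/22) = 1.36 degrees. A 2-degree imbalance is then 1.47 SE, with a two-sided probability of about 14% for a given pair, and it would move the change estimate by 0.3 × 2 = 0.6 degrees, 12% of the 5-degree target. This is the same variance loss seen within one trial and does not add to it.

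A reader might also infer that the baseline significance tests steer the analysis. The article attaches no decision to them, so they are a reporting matter only.

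**Conclusion.** The point holds as a loss of efficiency. The planned test is an unadjusted difference in change, and adjusting for a value that is already collected would lower the variance of the month-12 contrast by 15% (standard error by about 8%). This assumes ρ = 0.7, equal correlation and equal variances. Plausible departures take the gain from 25% down to a few per cent.

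Two stronger readings are not supported. The planned estimate is not biased. Nor is the trial underpowered because of this choice: with 22 per arm, power at α = 0.0167 is at least 90% under either reading of the SD, above the 80% target. The gain is material for power only if two conditions hold together: dropout brings arms near 13 (a loss of 1 − 13/22 = 41%), and 4.5 degrees is the SD of change. Power is then 67% as written and 75% with adjustment. Because the improvement is free, the wording is still worth changing.

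**What to change.** Use one of two near-equivalent models.

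1. Model months 3 to 12 as the outcome, with the baseline value of that outcome as a covariate next to treatment, time and site. The treatment effect is then the contrast between arms at the chosen visit, or averaged over visits. The treatment-by-time interaction would now test only whether that effect varies across follow-up, so the tested term has to be renamed.
2. Keep baseline in the outcome vector and fit one common baseline mean for all arms. With time as categories, removing the treatment main effect alone is not enough: for three arms and five visits the model keeps 15 columns of rank 15, the same saturated model with free baseline differences. The treatment-by-time terms at the baseline visit must also go, which leaves 5 + 2 × 4 = 13 mean parameters.

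State how time is coded. As a side matter, baseline characteristics can be presented without significance tests. The cost is a change of wording in the Statistics section; no new data or visits are needed.

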### Intervention/comparisons

Patients of the control group will receive their usual care which may include ankle-foot-orthoses (AFOs) that are worn during the day (for standing and walking), oral baclofen therapy or other tone-reducing medications, strength training, stretching exercises, physical therapy, occupational therapy etc. Changes in usual care during the study will be monitored using questionnaires. Children will drop out of the study if they need surgical treatment (orthopaedic and neurosurgical procedures affecting muscle tone and length), botulinum toxin A injections in the lower extremity or serial casting treatments in the lower extremity.

In addition to their usual care, patients of the experimental groups will be treated for one year with a static KAFO or with a dynamic KAFO using an Ultraflex^® ^ankle power unit. Children will be asked to wear the KAFO at least 6 hours per night. They will be allowed to remove the KAFO during the night when the child is seriously uncomfortable after wearing the KAFO for at least 20 minutes or when the child wakes up at night with complaints concerning the KAFO. When children do not wear the KAFO for 6 hours per night, parents will be asked to increase wearing time by asking the child to wear the KAFO during rest activities in day time. In case of unilateral treatment, patients will sleep one night with and one night without a KAFO. In case of bilateral treatment, patients will wear a KAFO alternating on the right and left side each night.

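### The intention-to-treat efficacy model adjusts for KAFO wearing time, which is the treatment received, so the KAFO-versus-control effect can be removed or attenuated depending on a coding the protocol does not fix

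*Protocol article*

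**What the plan says.** The Statistics section opens with "Statistical analysis will be performed according to an 'intention to treat' principle". It then describes one multi-level model for the primary and secondary outcomes, with group, time and site, and names the term that carries the treatment effect: "To test for any differences in the changes of variables between groups, a treatment*time interaction is included as independent variable". The covariates of that model follow: "Covariates will be: 1) KAFO wearing time, 2) lower leg growth, 3) use of an AFO by day", then stretching exercises and level of spasticity. None is labelled as secondary, per-protocol or explanatory, and no model without them is described.

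Other sections show what these variables are:

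- **Intervention/comparisons**, on the two KAFO arms: "Children will be asked to wear the KAFO at least 6 hours per night". Under Setting & design, the control group gets no additional intervention.
- **Protocol adherence**, on the source of the data: "These diaries will be filled in during the fourth week of each month and include questions regarding KAFO use, KAFO-related complaints, sleeping problems". The same diaries cover daytime AFO use and stretching.
- **Statistics** gives no time point for any covariate and does not say whether wearing time is a child-level mean, a time-varying value or interacted with time.

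**The concern.** An intention-to-treat contrast is the effect of being assigned a KAFO, whatever wear follows. Wearing time is a consequence of assignment and almost determines whether a child is in a KAFO arm. Once it is in the model, the group terms compare children at equal hours worn. Controls can supply such children only at zero hours, so the KAFO side of the comparison is an extrapolation.

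The protocol's own rationale makes this serious. Under Orthotic management in rest, protection is supposed to occur when the device is worn for six hours or more a day, and under Morphological properties the benefit is ascribed to longer slack length and lower stiffness of the muscle. Hours worn is thus the hypothesised route of the effect, and the model adjusts for that route. It also undoes part of the Withdrawal section, which keeps children with irresolvable KAFO problems in the analyses: their low wear would be retained and then adjusted for. The static-versus-dynamic comparison is exposed in the same way if the two devices are tolerated differently.

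At stake is the main result of the trial. An effective orthosis could be reported as ineffective, or as much less effective than it is.

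**Working it through.** **1. The plan's own figure.** From Sample size calculation: difference 5 degrees, SD 4.5, alpha 0.05/3 = 0.0167 (two-sided assumed), power 80%, five measurements, rho 0.7.

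n = 2 × [SD × (z(1−alpha/2) + z(power)) / difference]² × [1 + (T−1) × rho] / T

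- Without the repeated-measures factor: 2 × [4.5 × (2.394 + 0.842) / 5]² = 16.96.
- Factor: (1 + 4 × 0.7) / 5 = 0.76.
- 16.96 × 0.76 = 12.89, so 13 per group, as stated.

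The same formula gives power of 80.4% at 13 and 96.7% at 22 per group. It contains no covariates, so dropping wearing time leaves the sample size intact.

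**2. What each coding does.** Suppose all benefit runs through hours worn, at 5/6 degree per hour by month 12, with mean wear 6 h.

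- *Mean wear per child, main effect only.* Treatment*time rests on within-child change. With complete data, a covariate that is constant within a child cannot move it. The estimate stays at 5.
- *Wear plus wear-by-time.* The group*time term becomes the effect at zero hours: 5 − 6 × 5/6 = 0.
- *Time-varying wear (0 at baseline), categorical time, gradual benefit.* The wear slope averages over the visits at 3, 6, 9 and 12 months: (0.25 + 0.50 + 0.75 + 1.00) / 4 = 0.625 of its final size. What remains at 12 months is 5 × (1 − 0.625) = 1.9. If the benefit is immediate, nothing remains.
- *Time-varying wear, linear time, gradual benefit.* The straight-line group trend absorbs most of the benefit, so attenuation is small.

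**3. Simulation.** From the article: 3 × 22 children, five visits, SD 4.5, rho 0.7, effect 5 degrees, alpha 0.0167. Assumed, because the article does not give them: wear with mean 6 h and SD 1-2 h in the KAFO arms, 0 h in controls; all or half of the benefit through hours; no missing visits. Models were fitted by generalised least squares with compound symmetry. Each cell gives the KAFO-versus-control estimate in degrees, then power.

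| Coding of wearing time | All benefit through hours | Half through hours |
|---|---|---|
| Left out | 5.0; at least 98% | 5.0; at least 98% |
| Mean per child, main effect only | 5.0; at least 98% | 5.0; at least 98% |
| Time-varying, linear time, gradual benefit | 4.5-5.0; 97-100% | 4.7-4.9; 98-99% |
| Time-varying, categorical time, gradual benefit | 1.8-2.1; 4-14% | 3.4; 15-42% |
| Time-varying, categorical time, immediate benefit | about 0; 1-2% | 2.6; 9-20% |
| Wear plus wear-by-time | about 0; 1-2% | 2.4-2.5; 5-19% |

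Precision also suffers. With a gradual benefit wholly through hours, adding wear and wear-by-time raises the standard error from 0.9 to 3.2 degrees at wear SD 1 h, and from 1.0 to 1.7 at SD 2 h.

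**4. The other covariates.**

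- Daytime AFO use and stretching: the diaries, filled in monthly, "include questions regarding KAFO use, KAFO-related complaints, sleeping problems, the use of an ankle-foot orthosis (AFO) as well as questions regarding stretching exercises". Taken from there they are post-randomisation and could respond to an allocation that families know.
- Lower leg growth: a change over follow-up, so post-randomisation, but nothing in the article indicates that a KAFO alters it.
- Spasticity: part of the physical examination, with no time point given for the covariate. A baseline value would be unobjectionable.

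**The case against.** The strongest reply is that the tested term is treatment*time and that the article lists covariates without interacting them with time. Read literally, a child-level wearing time entered as a main effect leaves the tested term untouched, and a time-varying one with linear time barely changes it. This stands. A reader might infer that the planned model is bound to show no KAFO-versus-control difference however well the device works. The article does not support that: complete loss of a gradual benefit needs a wear-by-time term that is not stated. An unstated statistical analysis plan might also settle on a harmless coding.

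The wear distribution and the share of benefit through hours are not in the article either, so the sizes above are illustrations under stated assumptions.

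Three further inferences go too far:

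- *That all five covariates bias the comparison.* For lower leg growth no effect of treatment is shown, and there is a reason to consider it, since range of motion depends on muscle-tendon length relative to bone. Spasticity may be a baseline value, and current therapies are also asked about at intake. That AFO use and stretching respond to allocation is possible but not shown.
- *That the covariate defeats the blinding of the analyst* ("The researchers performing the measurements and analysing the data will be blinded with respect to the treatment allocation"). Hours worn would separate controls from KAFO users but not static from dynamic, and a dose-response analysis among KAFO users needs the same knowledge. This is a side issue.
- *That wear is zero in controls without exception.* Premature termination of the study allows controls to receive a KAFO after the interim evaluation.

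None of this makes wearing time suitable for a model presented as intention to treat. The harmless codings only fail to do damage, and the article does not choose among the codings.

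**Conclusion.** Wrong as written. The conflict between the intention-to-treat label and a covariate that measures treatment received is explicit in the Statistics section; it is a stated analysis, not an omitted detail. That conclusion needs no assumption.

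Its size does. With a true effect of 5 degrees, 22 per arm, alpha 0.0167, mean wear 6 h (SD 1-2 h) and all benefit through hours worn, the reported effect could lie anywhere from about 0 degrees with power of 1-2% to the full 5 degrees with power of at least 98%, according to a coding left open. If half the benefit runs through hours, the damaging codings give about 2.4-3.4 degrees with power of 5-42%. The supportable statement is that the adjustment can remove or attenuate the effect, not that it will.

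Wearing time is the main fault. Follow-up AFO use and stretching share it in a weaker form. Lower leg growth is a minor matter, and spasticity is none if measured at baseline.

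**What to change.** In the Statistics section, specify the primary and secondary efficacy models with treatment, time, treatment*time, site and baseline covariates only, for example baseline spasticity and baseline AFO use. State the time point of each covariate.

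Move KAFO wearing time, and AFO use and stretching taken from the follow-up diaries, to a separately labelled exploratory adherence or dose-response analysis, with wearing time analysed within the two KAFO arms. If lower leg growth is of interest, report it there as well.

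The cost is a change of wording. The same data are collected, and the calculated 13 and planned 22 per group are unaffected.
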